## Abstract

Rheumatoid arthritis (RA) is characterised by increased rates of cardiovascular disease (CVD), which represents the leading cause of death. Patients with RA presents increased prevalence of hypertension, which substantially contributes to the increased CVD burden associated with the disease. A solid pathophysiological background supports the presence of microvascular dysfunction in RA even in the absence of established CVD, while macrovascular dysfunction in the form of large artery stiffening has been further described. Janus kinase (JAK) inhibitors constitute a novel class of disease-modifying anti-rheumatic drugs (DMARDs) for the management of rheumatoid arthritis (RA). However, the vascular effects of JAK inhibitors in RA patients remain largely understudied. More recent evidence suggests higher risk of major adverse cardiovascular events with JAK inhibition compared to treatment with a TNF inhibitor, and calls for more careful consideration of potential negative effects on the cardiovascular system. The present prospective observational cohort study aims to investigate the impact of JAK inhibitors on ambulatory blood pressure and haemodynamic profile, as well as markers of micro- and macrovasculopathy among patients with RA.

## INTRODUCTION

Rheumatoid arthritis (RA) is the most prevalent autoimmune rheumatic disorder characterised by increased rates of cardiovascular complications, which represent the leading cause of death in these patients.^1,2^ Microvascular endothelial dysfunction represents a primary mechanistic model for the development and progression of cardiovascular disease (CVD), as it precedes and accelerates large artery dysfunction, systemic atherosclerosis, and related risk factors. A solid pathophysiological background supports the presence of vascular dysfunction in RA, which is detected even in the absence of established CVDs.^3–5^ Dysregulation of autoimmunity and cumulative inflammatory load in RA leads to overexpression of adhesion molecules, pro-thrombotic, and pro-inflammatory factors, which in turn increase vascular smooth muscle cell proliferation and tone and promote the development of atherosclerosis.^6^ Indeed, patients with RA show impaired vascular biomarkers such as flow-mediated dilation (FMD) of the brachial artery.^7^ Furthermore, elevated levels of circulating biomarkers of thromboinflammation and endothelial dysfunction in patients with autoimmune inflammatory diseases suggest that an ongoing vasculodestructive process is already underway despite the absence of clinical evidence of CVD.^8^

While microvascular endothelial dysfunction is considered inherent to the disease, patients with RA present increased prevalence of traditional CVD risk factors.^9^ Among these patients, hypertension represents the most prevalent CVD risk factor and significantly aggravates cardiovascular prognosis.^10^ Despite major implications in terms of CVD development and progression, hypertension remains largely underdiagnosed and undertreated in patients with RA.^11^ Furthermore, the impact of anti-rheumatic treatment is often neglected and needs to be further taken into consideration. Antirheumatic treatment modalities exert divergent effects on the vasculature, with positive, neutral, or even negative effects which further contribute to the CVD complications associated with RA. While these effects have been well-described or are being intensively investigated for cornerstone treatments such as corticosteroids or biologics, the vascular effects of novel antirheumatic treatments, such Janus kinase (JAK) inhibitors, remain in comparison understudied.^12,13^ Ultimately, chronic inflammation, traditional CVD risk factors and, to a different extent, specific antirheumatic treatment modalities act synergistically to form a prothrombotic microenvironment and trigger the degeneration and remodelling of the vascular architecture.

## JAK INHIBITION AND CARDIOVASCULAR COMPLICATIONS

JAK inhibitors are the newest drug class of disease-modifying medication that have been approved for the treatment of RA. Their mechanism of action is based on the modification of the signal transducer and activator of transcription (STAT) constituents in cytokine signalling, which is implicated in the pathogenesis of RA. As a targeted low molecular mass drug that can pass the lipid bilayer of the cellular membrane, they offer the first long-term oral biologic option in RA.^14^ In the 2019 updated European League Against Rheumatism (EULAR) recommendations for the management of RA with synthetic and biological disease-modifying antirheumatic drugs (DMARDs), it is recommended to add any biological DMARD or JAK inhibitor on top of conventional synthetic DMARDs upon presence of poor prognostic factors (presence of autoantibodies, high disease activity, early erosions or failure of two csDMARDs). Potential safety concerns secondary to JAK inhibition include a higher risk of herpes zoster infections and venous thromboembolic events (deep vein thrombosis, pulmonary embolism).^15^ With regard to the latter, the effects of JAK inhibitors on the cardiovascular system are being thoroughly investigated and have not yet been specified in detail. A systematic review and meta-analysis of randomised controlled trials indicated no significant change in cardiovascular risk for patients with RA treated with JAK inhibitors at least in a short-term perspective.^16^ Nevertheless, the recent ORAL Surveillance trial comparing the combined tofacitinib doses with a TNF inhibitor in a cardiovascular risk–enriched population with RA showed higher risks of major adverse cardiovascular events and cancer with the JAK inhibitor than with a TNF inhibitor.^17^ No apparent mechanism of action has been proposed or proven currently for this safety signal.^18^ Despite their efficacy in the suppression of RA-related inflammation, treatment with JAK inhibitors may negatively affect CVD risk factors, such as platelet count and lipidemic profile.^19^ By contrast, data remain scarce regarding the impact of JAK inhibitors on blood pressure, especially ambulatory blood pressure, haemodynamic profile, and markers of micro- and macrovasculopathy among patients with RA. Notably, both the macrovasculature and the microvascular network in RA can be easily assessed by use of non-invasive techniques that are being widely applied in the field of CVDs, such as assessment of arterial stiffness and nailfold videocapillaroscopy (NVC), respectively.

## 24H AMBULATORY BLOOD PRESSURE

24h ambulatory blood pressure is a powerful predictor of CVD morbidity and mortality in the general population and in high CVD risk populations.^20^ Its predictive value in terms of cardiovascular health is superior to the conventional office blood pressure measurements, as stated in current hypertension guidelines.^21^ Patients with RA present increased prevalence of hypertension, which along with smoking confers the highest CVD risk of all traditional CVD risk factors in this specific group of patients.^9^ They additionally present disturbed abnormal blood pressure rhythm, with increased prevalence of nocturnal hypertension and disturbed nocturnal blood pressure drop (non-dipping).^22^ Remarkably, the newest devices for ambulatory blood pressure monitoring can simultaneously record haemodynamic parameters throughout the whole 24h period, including central (aortic) blood pressure, wave reflection, total vascular resistance, as well as markers of arterial stiffness such as augmentation index (AIx) and pulse wave velocity (PWV).

## ARTERIAL STIFFNESS AS A SURROGATE CVD RISK MARKER

Arterial stiffness is defined as the loss of arterial elasticity and compliance subsequent to mechanical and structural changes of the vascular wall. The gold-standard marker of arterial stiffness is measurement of PWV, which corresponds to the rate at which pressure waves travel downstream through the arterial wall.^23^ Other markers of arterial stiffness include the assessment of AIx from the analysis of the wave reflections, and pulse pressure calculated by subtracting diastolic blood pressure from systolic blood pressure.^24^ Data from tenths of thousands of individuals have established the prognostic value of arterial stiffness in terms of CVD risk prediction.^25^ Arterial stiffness is closely associated with traditional CVD risk factors, predominantly age and hypertension.^24^ Increased PWV is an independent predictor of CVD morbidity and mortality in the general population and high risk patients such as those with hypertension, type 2 diabetes mellitus, end-stage renal disease, and elderly individuals.^25,26^ Its predictive value not only remains significant even after adjustment for Framingham risk score,^27^ but also enhances the utility of current risk prediction models when added on top of classical CVD risk factors.^28^ Arterial stiffness in RA has been addressed in several studies, with the majority concluding that markers of arterial stiffness are increased in RA individuals. However, whether and to which extent increased arterial stiffness in RA reflects the increased prevalence of traditional CVD risk factors or the consequences of chronic inflammation remain under investigation.^29^ Furthermore, the impact of novel antirheumatic treatments including JAK inhibitors on arterial stiffness remains unclear.

## NVC AS MARKER OF MICROVASCULAR HEALTH AND DISEASE

The dermal capillary network represents an “open window” for the study of the microcirculation. NVC has been widely applied as a bedside aid in rheumatology, especially in the diagnosis and follow-up of patients with systemic sclerosis. In these patients, peripheral microvascular abnormalities detected with NVC reflect the severity of visceral organ involvement^30^ and correlate with the presence of pulmonary arterial hypertension^31^ and as markers of CVD risk, such as arterial stiffness^32,33^ and increased levels of uric acid.^34^ Capillaroscopic microvascular abnormalities are also common in patients with CVDs. Evaluation of NVC in autoimmune rheumatic diseases has been proposed as a potential tool for the prediction of microvascular heart involvement,^35^ while preliminary data have shown that capillary abnormalities correlate with CVD risk, either as an individual marker in high-risk patients^36^ or in combination with other microvascular indices in low-to-moderate risk hypertensive patients.^37^ Several patterns of capillaroscopic abnormalities have been previously described with NVC in patients with diabetes mellitus including capillary dilatation, avascular zones and tortuous capillaries,^38^ while presence of diabetes mellitus further aggravates structural and functional capillary density in patients with chronic kidney disease.^39^ Capillary rarefaction is particularly common in patients with hypertension, both as a cause and consequence of high blood pressure.^40^ Last but not least altered capillaroscopic parameters indicative of peripheral microangiopathy have been described in patients with pulmonary arterial hypertension associated with various autoimmune diseases^41^ or due to congenital heart disease,^42^ and chronic thromboembolic pulmonary hypertension.^43^ Dermal capillary alterations detected with NVC and their clinical significance are being thoroughly investigated in patients with RA and have been summarized in detail elsewhere.^44^

## AIM OF THE STUDY

The present study aims to provide further insight on the effects of treatment with JAK inhibitors on blood pressure and haemodynamic parameters, microvascular function, and subclinical macrovascular injury among patients with RA. More specifically, we aim to investigate whether treatment with JAK inhibitors in patients with RA induces alterations in:
24h BP and its circadian rhythmArterial stiffness, specifically AIx and PWV which represent the most widely used markers of large artery stiffening.Microangiopathy of the nailfold capillaries.Patients’ haemodynamic profile throughout a whole 24h period (central aortic blood pressure, wave reflection, total vascular resistance)Prothrombotic markersEstimated cardiovascular risk

## METHODS

### Study design and setting

This is a prospective, observational cohort study, that will be conducted by the Fourth Internal Medicine Department at Hippokrateion General Hospital of Thessaloniki in collaboration with the Second Medical Department of the same hospital.

### Inclusion criteria

This study enrols adult patients with an established diagnosis of RA according to the American Rheumatism Association 1987 Revised Criteria,^45^ who are eligible for treatment with JAK inhibitors (tofacitinib, baricitinib or upadacitinib) for first time, irrespective of previous administration of conventional or biologic DMARDs based on international recommendations (EULAR 2020).^15^

Exclusion criteria include: age <18 years, inability to comprehend and sign the informed consent, previous exposure to JAK inhibitors, concomitant active malignancy or other disease with poor prognosis, recent major adverse cardiovascular event (myocardial infarction, unstable angina, stroke) within the past 6 months, and stage III–IV heart failure according to the New York Heart Association (NYHA) criteria.^46^

### Study overview

RA patients eligible for treatment with JAK inhibitors who will be selected on the basis of inclusion and exclusion criteria to participate in the research protocol will undergo the following procedures, before the initiation of JAK inhibitors:
Recording of medical history and current medical treatmentAnthropometric measurements, clinical examination and assessment of disease severity with calculation of DAS28 (Disease Activity Score in 28 joints)Evaluation of functional ability and quality of life through specifically designed questionnairesOffice blood pressure recordingEstimation of 10-year cardiovascular riskVideocapillaroscopy of the nailfold capillary networkAssessment of 24h blood pressure, its day- to night-time variation and haemodynamic parameters with the Mobil-O-Graph deviceBlood sampling, centrifugation and thawing of the supernatant

All patients will be re-evaluated and the above procedures will be repeated at 3 and 6 months following the baseline visit, whilst the patients are under treatment with JAK inhibitors.

### Study procedures

#### Measurement of blood pressure, arterial stiffness, and haemodynamic parameters

24h blood pressure recording is recommended as the ideal method of BP monitoring according to current hypertension guidelines.^21^ The Mobil-O-Graph (IEM, Stolberg, Germany) device will be applied to all participants, which has been approved by Food and Drug Administration (FDA) and the European Union and has been validated according to the protocols of the European and the British Society of Hypertension^47,48^. Automatic BP readings will be performed at 20-min intervals during the day and at 30-min intervals during the night. Only ABPM reports with a minimum of 70% successful readings will be regarded as technically sufficient. Mean 24h, day- and night-time BP will be obtained, as well as the nocturnal fall in BP (%), also defined as “% dipping”. According to the dipping values, individuals will be classified as “dippers” (≥10%) and “non-dippers” (<10%).

Moreover, arterial stiffness indices (PWV, AIx) and haemodynamic parameters (central [aortic] systolic, diastolic and mean blood pressure, pulse pressure, total vascular resistance, and reflection coefficient) are simultaneously obtained at each blood pressure measurement. The mean values of the above markers will be included in the analysis.

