## STUDY OUTCOMES

### Primary outcomes

To determine potential differences at 3 and 6 months following treatment with JAK inhibitors compared to baseline, in the following parameters: a) 24h BP, b) arterial stiffness, c) microangiopathy of dermal capillary network, d) prothrombotic markers.

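### The 70% acceptance rule pools day and night readings, so a recording with few or no night readings can count as technically sufficient

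*Protocol article*

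**What the plan says.** All the relevant rules stand in the protocol article, in the section on measurement of blood pressure, arterial stiffness and haemodynamic parameters.

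- Schedule: "Automatic BP readings will be performed at 20-min intervals during the day and at 30-min intervals during the night".
- Acceptance: "Only ABPM reports with a minimum of 70% successful readings will be regarded as technically sufficient".
- BP quantities derived: "Mean 24h, day- and night-time BP will be obtained, as well as the nocturnal fall in BP (%), also defined as “% dipping". Patients are then classed as dippers (a nocturnal fall of 10% or more) or non-dippers.
- Stiffness and haemodynamic markers "are simultaneously obtained at each blood pressure measurement. The mean values of the above markers will be included in the analysis".

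The Primary outcomes section looks for change at 3 and 6 months from baseline "in the following parameters: a) 24h BP, b) arterial stiffness, c) microangiopathy of dermal capillary network, d) prothrombotic markers". The Aim of the Study lists 24h BP together with its circadian rhythm. No section gives a minimum number or share of night readings, or the clock hours that count as day and night.

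**The concern.** The rule is meant to secure the quantities computed from an accepted recording, and several of these depend on the night. Because readings are denser by day, the day can meet a pooled 70% with little or no help from the night. A recording may then be called sufficient although night BP and dipping cannot be computed, or rest on a handful of readings. Its 24h mean would in substance be a daytime mean. The same holds for PWV and AIx, which are taken from the same readings.

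The comparison is within patient, between visits, in 30–50 patients without a control group. A visit whose 24h value mainly describes the day is not like-for-like with one that covers the night.

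**Working it through.** **Inputs.** From the document: 3 readings per hour by day, 2 per hour by night, threshold 70% of all readings. Assumed, because the document gives no hours: a night of x hours. The 70% is a stated rule, not a derived figure, so there is nothing to reproduce first.

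**Step 1: when can the day pass alone?** Scheduled readings are 3(24 − x) by day and 2x by night, in total 72 − x. A complete day with an empty night passes if

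3(24 − x) / (72 − x) ≥ 0.70, so 72 − 3x ≥ 50.4 − 0.7x, so x ≤ 21.6 / 2.3 = 9.39 hours.

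| Night (h) | Day + night = total | Needed for 70% | Day share | Day readings needed if no night reading | Night readings needed if day complete |
|---|---|---|---|---|---|
| 6 | 54 + 12 = 66 | 47 | 81.8% | 47 of 54 (87%) | 0 |
| 7 | 51 + 14 = 65 | 46 | 78.5% | 46 of 51 (90%) | 0 |
| 8 | 48 + 16 = 64 | 45 | 75.0% | 45 of 48 (94%) | 0 |
| 9 | 45 + 18 = 63 | 45 | 71.4% | 45 of 45 (100%) | 0 |
| 10 | 42 + 20 = 62 | 44 | 67.7% | cannot pass | 2 of 20 |
| 12 | 36 + 24 = 60 | 42 | 60.0% | cannot pass | 6 of 24 |

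**Step 2: partial loss of the night (8-hour night, 45 needed).**

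- 0 of 16 at night: passes with 45 of 48 by day (94%).
- 4 of 16 at night: passes with 45 − 4 = 41 of 48 by day (85%).
- 8 of 16 at night: passes with 45 − 8 = 37 of 48 by day (77%).

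Losing half or three quarters of the night therefore does not require a near-perfect day.

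**Step 3: illustration for the 24h mean.** Two further assumptions, neither in the document: the 24h mean is a plain average of readings, and systolic BP is 15 mmHg lower at night. With a complete day and k night readings lost at one visit, that visit's mean shifts by

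15 × (48/(64 − k) − 48/64).

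- k = 8: 15 × (0.857 − 0.750) = 1.6 mmHg
- k = 12: 15 × (0.923 − 0.750) = 2.6 mmHg
- k = 16: 15 × (1.000 − 0.750) = 3.75 mmHg

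The shift is proportional to the gap: at 10 mmHg it is 1.1, 1.7 and 2.5 mmHg. These are shifts for one patient at one visit. One recording with an empty night, at one visit only, moves the cohort mean change by 3.75/50 = 0.08 to 3.75/30 = 0.13 mmHg.

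**The case against.** The case against has several parts.

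- *The night hours are not given.* This stands. An empty night passes only up to about 9.4 hours, and needs 94% day success at 8 hours and 100% at 9. The calculation shows what the rule permits, not what a usual recording looks like. With a 10-hour night, however, 2 of 20 night readings are still enough.
- *The averaging method is not stated.* This stands. A reader might infer that the plan under-weights the night by averaging all readings plainly. The article says only that means will be obtained and analysed, so that is not established. Even under plain averaging, a constant weighting offset largely cancels in within-patient change. The mmHg figures are therefore illustrations. The gap in the acceptance rule does not depend on them.
- *Nothing shows that failures concentrate at night.* This stands. No failure rates by period are given. The point needs only that the rule would not detect such losses.
- *The rule is a necessary condition, and a fuller protocol may add a night minimum.* This is possible, but the article gives no other criterion. It chose to state an acceptance rule and then listed quantities which that rule does not protect. This is a rule fixed badly, not a detail left out in condensing.
- *With no night readings, no false dipping value arises, and dipping is not a listed outcome.* Both are true. The dipping problem lies in values from very few readings, and it touches a stated aim. The 24h mean and the averaged stiffness markers remain, and these do serve listed primary outcomes.

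**Conclusion.** The point holds as a weakness in a stated rule. On the document's own intervals, the pooled 70% can be met without any night reading for nights up to about 9.4 hours. For an assumed 8-hour night it can be met with a quarter of the night readings and 85% of the day readings. Night BP and dipping are then incalculable or unreliable, and the 24h BP, PWV and AIx are mainly daytime values at that visit.

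The effect on the outcomes is added noise in the change from baseline, and bias only if night completeness differs systematically between visits. A reader might conclude that the change in 24h BP will be biased upwards. The documents do not support this. If BP falls at night, lost night readings raise the mean at the affected visit, so losses at baseline push the change down and losses at follow-up push it up. The direction also presumes a nocturnal fall, while the article itself reports more non-dipping in RA.

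This is worth correcting before analysis, but nothing shows that it would overturn a result.

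**What to change.** Fix the day and night hours in advance and apply the 70% minimum to the scheduled readings of each period separately. For a 16h/8h split this means at least 34 of 48 by day (0.70 × 48 = 33.6) and 12 of 16 by night (0.70 × 16 = 11.2). Use night BP, percentage dipping and dipper class only when the night minimum is met. Use 24h means of BP, PWV, AIx and the haemodynamic parameters only when both minima are met. If the full protocol already has such a rule, cite it.

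The total then required is 34 + 12 = 46 of 64, one more than now. What changes is where the readings must lie.

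An optional safeguard is to compute 24h means from the day and night means weighted by hours. Under plain averaging, the night share of accepted readings could still range from 12/60 = 20% to 16/50 = 32%. At an assumed 15 mmHg gap and against 25% for a complete recording, that is a shift between 15 × (0.25 − 0.32) = −1.05 and 15 × (0.25 − 0.20) = +0.75 mmHg. Weighting by hours removes it.

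The cost is a sentence or two in the protocol and a recalculation from stored readings. Some recordings will lose their night or 24h values. How many cannot be estimated from the article, and in 30–50 patients each loss counts, so the number excluded at each visit should be reported.
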